### Blinding procedure

The study medication is blinded to both study participants and the investigators. If un-blinding of one or more study participants is required, Glostrup Pharmacy hold the randomization list and can be contacted 24 h a day. Furthermore, the investigators have a sealed envelope with the randomization list, if there is a need for un-blinding of any participants. To minimize the risk of participants comparing experiences, the study visits will be arranged staggered throughout the day and always separately. When all study participants have completed the trial, the study medication will be un-blinded.

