### Randomization

Participants will be randomized to NAC or placebo treatment by a computer-based random eight block number generator. The study participants will be randomised sequentially by the order they are enrolled into the trial. The randomization assignments will be hidden from the participants and the study investigators and raters. An independent pharmacy, Glostrup Pharmacy, will perform the randomization process, provide the randomization codes and the labelling of the tablet containers. The Coordinating Investigator ([name]) and Sponsor/Principal Investigator ([name]) will enrol and assign participants from two of the study centres, and the second Principal Investigator ([name]) and a project nurse ([name]) will enrol and assign participants from the latter study centre.

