### Outcome measures

The clinical and demographic data is obtained by the investigators through patient interviews and from hospital records. The biological data is obtained through laboratory analyses of blood and urine samples. An overview of the data collection process is displayed in Table 1.

**Table 1 Tab1:** Overview of all measurements, instruments and time points

Variables	Sources	Study period					
		Enrolment	Intervention				Follow-up
		Screening	Baseline (week 0)	Visit 2 (week 2)	Visit 3 (week 10)	Visit 4 (week 20)	Visit 5 (week 24)
MADRS	Rater	X		X	X	X	X
MES, WHO-5, GAF-S, GAF-F, CGI-S YMRS	Rater/self-reported		X	X	X	X	X
M.I.N.I.-Interview	Rater	X					
Demographic (age, gender, height, inclusion site, etc.)	Self-reported		X				
Weight and BMI	Rater		X	X	X	X	X
Personal and demographic details (income source, education, relationship etc.)	Self-reported		X				
Family mental history	Self-reported		X				
Lifestyle information (smoking status, alcohol consumption and substance abuse)	Self-reported		X	X	X	X	X
Disorder information (no. of: episodes of depression, hypomania/mania, neutral mood, ECT, hospital admissions, suicidal thoughts, suicide attempts, etc.)	Self-reported/hospital record		X				
Medical conditions (Doctor diagnosed)	Self-reported		X				
Pharmacological treatment	Hospital record		X	X	X	X	X
Psychological treatment	Self-reported		X	X	X	X	X
Adverse events/reactions	Self-reported		X	X	X	X	X
Biography	Self-reported			X			
Urine samples	Laboratory		X	X	X	X	X
Blood samples	Laboratory		X			X	X
DNA	Laboratory		X			X	X

*Screening* pre-intervention, *Baseline* pre-intervention (week 0), *Visit 2* week 2, *Visit 3* week 10, *Visit 4* post-intervention (week 20), *Visit 5* follow-up (week 24), *Rater* coordinating investigator/project nurse, *MADRS* Montgomery-Åsberg Depression Rating Scale score, *MES* Bech-Rafaelsen Melancholia Scale, *WHO-5* World Health Organization well-being index, *GAF-S* The Global Assessment of Symptoms scale, *GAF-F* The Global Assessment of Functioning scale, *YMRS* Young Mania Rating Scale (YMRS), *CGI-S* The Clinical Global Impression-Severity scale (CGI-I), *M.I.N.I-interview* Mini International Neuropsychiatric Interview, *ECT* electroconvulsive therapy

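### The investigators' backup for breaking the code is the randomisation list itself, so opening it for one participant would also reveal other past and future allocations

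*Protocol article*

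**What the plan says.** The protocol article covers this point in four places.

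- **Randomization.** The sequence comes from a "computer-based random eight block number generator" run by an independent pharmacy. On order of allocation: "The study participants will be randomised sequentially by the order they are enrolled into the trial". On concealment: "The randomization assignments will be hidden from the participants and the study investigators and raters". The coordinating investigator and the sponsor/principal investigator "will enrol and assign participants from two of the study centres"; a second principal investigator and a project nurse do so at the third.
- **Blinding procedure.** Two routes for un-blinding are given. The first is the pharmacy: "Glostrup Pharmacy hold the randomization list and can be contacted 24 h a day". The second is local: "the investigators have a sealed envelope with the randomization list, if there is a need for un-blinding of any participants". No order of preference between the two is set. General un-blinding is planned only once every participant has finished.
- **Outcome measures, legend to Table 1.** The rater is defined as "coordinating investigator/project nurse", and the MADRS is listed as rater-assessed.
- **Discussion.** The use of only two raters is named as a strength, alongside the double-blind design.

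**The concern.** An emergency code-break should tell the person who needs it what one participant received, and nothing more. A list cannot do that. Whoever opens it sees the other participants' allocations too and, where allocation is sequential, the assignments waiting for people not yet enrolled.

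Two protections are at stake. The first is allocation concealment: someone who knows the next assignment can, even without meaning to, let it influence whom to enrol and when. The second is blinded assessment: the primary outcome is change on the MADRS, which a rater scores by judgement, and there are only two raters. In this trial the same small group enrols and rates, so one opening could affect both.

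**Working it through.** The plan states no figure to reproduce here. The check is a reading of the sections together, followed by a simple count.

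**Step 1: what the envelope contains.** The Blinding procedure section uses the same term, the randomization list, for what the pharmacy holds and for what is in the investigators' envelope. The article describes no per-participant code envelopes. Read as printed, the local backup is the list.

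**Step 2: what an opening reveals.** Allocation follows the order of enrolment into the trial, so the unused entries are the future assignments. Inputs: planned recruitment N = 78 (Sample size and feasibility of recruitment); k = number enrolled when the envelope is opened, including the participant to be un-blinded.

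- Other allocations already made: k − 1
- Allocations still to come: N − k
- Total beyond the one needed: (k − 1) + (78 − k) = 77, whatever k is

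| Opened after k enrolled | Other past allocations (k − 1) | Future allocations (78 − k) |
|---|---|---|
| 10 | 9 | 68 |
| 39 | 38 | 39 |
| 60 | 59 | 18 |

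The timing changes the kind of damage. An early opening mainly threatens concealment of later enrolments. A late one mainly threatens the blinding of people already in the trial, to the extent that they still have ratings to come.

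**Step 3: who would see it.** The Randomization section and the Table 1 legend, set side by side:

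| Role | Enrols | Rates MADRS | Consequence if this person opens the list |
|---|---|---|---|
| Coordinating investigator | yes | yes | concealment and assessor blinding both at risk |
| Sponsor/principal investigator | yes | not in the rater definition | concealment at risk; rater blinding not automatically lost |
| Second principal investigator | yes | not in the rater definition | as above |
| Project nurse | yes | yes | both at risk, but the text gives the envelope to investigators and does not call the nurse one |

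Every named investigator enrols, so an opening by any of them bears on concealment. Assessor blinding is affected directly only if the opener rates.

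**Step 4: the other route.** The pharmacy holds the same list and can be reached around the clock. It can disclose one participant's allocation and leave the other 77 hidden. The exposure therefore comes from what the backup contains, not from code-breaking as such.

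**The case against.** The strongest reply is that this is a loosely worded sentence in a condensed article. The envelope may be shorthand for individual codes. Custody rules, intactness checks and code-break logs usually sit in the full protocol, which is not shown. That stands as regards the missing detail: the absence of a log or an envelope check is no finding. It does not dispose of the sentence itself, which states that the envelope holds the list and uses the same term for the pharmacy's copy.

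Several stronger conclusions are tempting, and the article does not support them:

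- *Any code-break exposes everyone.* No. The pharmacy is named first and need release only one allocation. The exposure follows only from opening the envelope.
- *The two sections contradict each other.* No. A sealed list is still hidden from the person who keeps it. The promise of concealment fails on opening, not on custody.
- *The damage could not be repaired.* Only in part. The pharmacy could issue a new list for participants not yet enrolled, and an unexposed rater could take over later ratings. Allocations already seen stay seen.
- *The envelope adds nothing but risk.* No. A local backup has value if the pharmacy cannot be reached. The problem is its format.
- *Most remaining ratings would be unblinded.* This cannot be shown. Enrolment by centre is not given, and the article does not say which investigator keeps the envelope.

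It is also fair that openings may never happen. The Discussion describes the study drug as well tolerated, and the discontinuation criteria do not require un-blinding. No frequency of code-breaks can be derived from the article.

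**Conclusion.** The point holds as a conditional weakness. If the investigators' envelope is opened for one participant, up to 77 other planned allocations become visible to someone who enrols and may also rate the primary outcome. If the pharmacy route is used instead, none of them need be.

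This rests on three assumptions:

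- The sentence means what it says, so the envelope contains the list and not individual codes.
- The list covers the whole trial in order of enrolment, as the Randomization section suggests. If each centre held only its own part, the exposure would be limited to that centre's share, which is not stated.
- Planned recruitment of 78 is met. The figure of 77 is an upper bound on exposure given an opening, not an expected loss.

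The number of copies of the envelope is not stated, but more copies would not lessen the problem. No analysis, estimate or sample size changes unless an opening occurs. It should be fixed because the safeguard is cheap and the failure, once it happens, is only partly reversible. It is not a defect that must be cured before the design can be accepted.

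**What to change.** Amend the Blinding procedure section in two respects:

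1. Codes are broken one participant at a time through the pharmacy's existing 24-hour service, as the first route.
2. The list held by the investigators is replaced by individually sealed, numbered, opaque envelopes, one per participant, each holding only that participant's allocation and kept as the local backup.

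If individual envelopes are already in use, correcting the sentence to say so is enough.

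The cost is a short amendment and some preparation work for the pharmacy, which already holds the list and labels the containers. Emergency access is preserved by both routes. Sample size, endpoints, visits and study treatment are unchanged.

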### Study treatment

Participants will be randomized to receive either NAC (National Center for Biotechnology Information 2017) or placebo in addition to their current pharmacotherapy and psychotherapy.

The study treatment powder (NAC and placebo) are imported and manufactured at Glostrup Pharmacy, which has manufacturing authorization, and all medication used is manufactured in accordance with good manufacturing practice (GMP) and good distribution practice (GDP).

The study medication is divided into nine, white containers containing 100 tablets each. The study medication is distributed twice during the 20 weeks, and receive 9 containers in total.

Participants will take three tablets containing 500 mg each, twice daily (3 g daily) for 20 weeks. NAC and placebo tablets have a similar appearance and have an added lemon odour, in order to camouflage the sulphur-containing odour of NAC.

ECT is not permitted 4 weeks prior to inclusion, but is allowed during the trial. Treating clinicians are allowed to change both psychopharmacy and psychotherapy during the trial at their discretion.

### Treatment adherence

To enhance adherence, the participants will be offered a text message with two daily reminder messages on taking the study medication. The participants will be encouraged to return all remaining trial medication at the end of study participation. The returned tablet containers and the tables will all be counted and documented.

### Outcome measures

The clinical and demographic data is obtained by the investigators through patient interviews and from hospital records. The biological data is obtained through laboratory analyses of blood and urine samples. An overview of the data collection process is displayed in Table 1.

**Table 1 Tab1:** Overview of all measurements, instruments and time points

Variables	Sources	Study period					
		Enrolment	Intervention				Follow-up
		Screening	Baseline (week 0)	Visit 2 (week 2)	Visit 3 (week 10)	Visit 4 (week 20)	Visit 5 (week 24)
MADRS	Rater	X		X	X	X	X
MES, WHO-5, GAF-S, GAF-F, CGI-S YMRS	Rater/self-reported		X	X	X	X	X
M.I.N.I.-Interview	Rater	X					
Demographic (age, gender, height, inclusion site, etc.)	Self-reported		X				
Weight and BMI	Rater		X	X	X	X	X
Personal and demographic details (income source, education, relationship etc.)	Self-reported		X				
Family mental history	Self-reported		X				
Lifestyle information (smoking status, alcohol consumption and substance abuse)	Self-reported		X	X	X	X	X
Disorder information (no. of: episodes of depression, hypomania/mania, neutral mood, ECT, hospital admissions, suicidal thoughts, suicide attempts, etc.)	Self-reported/hospital record		X				
Medical conditions (Doctor diagnosed)	Self-reported		X				
Pharmacological treatment	Hospital record		X	X	X	X	X
Psychological treatment	Self-reported		X	X	X	X	X
Adverse events/reactions	Self-reported		X	X	X	X	X
Biography	Self-reported			X			
Urine samples	Laboratory		X	X	X	X	X
Blood samples	Laboratory		X			X	X
DNA	Laboratory		X			X	X

*Screening* pre-intervention, *Baseline* pre-intervention (week 0), *Visit 2* week 2, *Visit 3* week 10, *Visit 4* post-intervention (week 20), *Visit 5* follow-up (week 24), *Rater* coordinating investigator/project nurse, *MADRS* Montgomery-Åsberg Depression Rating Scale score, *MES* Bech-Rafaelsen Melancholia Scale, *WHO-5* World Health Organization well-being index, *GAF-S* The Global Assessment of Symptoms scale, *GAF-F* The Global Assessment of Functioning scale, *YMRS* Young Mania Rating Scale (YMRS), *CGI-S* The Clinical Global Impression-Severity scale (CGI-I), *M.I.N.I-interview* Mini International Neuropsychiatric Interview, *ECT* electroconvulsive therapy

#### Clinical outcome measures

The clinical measurements include scales of depressive symptoms (MADRS and MES), manic symptoms (YMRS), quality of life (WHO-5), symptoms- and social functioning level (GAF-S and GAF-F) and global clinical impression (CGI-S). All rating scales used in the study are assessed and validated in Danish.

#### Biological outcome measures

The biological data collected from the study participants will include urine and blood samples as well as DNA. The biological data will be applied to investigate markers of oxidative stress and inflammation. All biological materials (urine, blood and DNA) will be collected from not-fasting participants. The urine and blood samples are transferred to tubes, and all three biological materials are stored in hospital freezers until analysis.

### Serious adverse reactions/events and adverse reactions/events

SARs, SAEs, Adverse Events (AE) and Adverse Reactions (AR) are defined according to good clinical practice (GCP), and assessed at each visit. Participants who discontinue study participation due to SAEs or SARs will be followed until the SAE/SAR has disappeared or the SAE/SAR is stable. Participants will be contacted with a few days after SAE/SAR and again after 4 weeks.

### Data management

The trial is conducted in accordance with good clinical practice guidelines and Declaration of Helsinki, and will be monitoring by the GCP-unit at Odense University Hospital, Denmark. The study is approved before study initiation by the Regional Scientific Ethical Committees for Southern Denmark: 35664-20120177, the Danish Medicines Agency: 2012-004483-22, and Danish Data Protection Agency: 2008-58-0035. The trial is registered at ClinicalTrials.Gov: NCT02294591 and the European Clinical Trials Database, EudraCT: 2012-004483-22.

All data in the CRFs (Case Report Forms) are double entered in the database program *Research Electronic Data Capture* (REDCap) (Harris et al. 2009) by coordinating investigator ([name]).

### Sample size and feasibility of recruitment

The sample size estimation was based on prior data from a similar clinical trial showing mean (SD) in MADRS score (from baseline to end of the study (week 24)) was decreased by around 10.0 ± 4.3 and increased by around 0.9 ± 2.6 (in respectively the NAC and the placebo group (Berk et al. 2008). Our sample size was calculated using a two-tailed independent sample t-test with 80% power to detect baseline-adjusted between-group mean difference at week 20, and a two-sided alpha-level of 0.05. To detect a between-group mean difference of change from baseline of at least 8 ± 10.0, 56 participants in total were required. Due to the expectation of a 40% drop-out rate we aim to recruit an overall of 78 study participants. To achieve an adequate number of participants, all in- and out-patients from the Mental Health Service included in the study having a bipolar disorder or suspect to have this disorder, are offered to participate.

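### The target of 78 does not allow for the stated 40% drop-out: about 47 would remain, not 56, and t-test power is about 76%, not 80%

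*Protocol article*

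**What the plan says.** All the figures stand in the protocol article under *Sample size and feasibility of recruitment*. The calculation rests on a "two-tailed independent sample t-test with 80% power to detect baseline-adjusted between-group mean difference at week 20", with "a two-sided alpha-level of 0.05". The requirement follows: "To detect a between-group mean difference of change from baseline of at least 8 ± 10.0, 56 participants in total were required". The allowance for losses comes next: "Due to the expectation of a 40% drop-out rate we aim to recruit an overall of 78 study participants". No formula for the step from 56 to 78 is shown, and nothing elsewhere in the article revises any of these numbers.

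The allocation ratio is not stated. The *Randomization* section says only: "Participants will be randomized to NAC or placebo treatment by a computer-based random eight block number generator". I take this as equal allocation to two arms.

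**The concern.** If 56 people must be evaluable at week 20 and 40% are expected to be lost, the number recruited times 0.6 has to reach 56. For 78 it does not. The requirement, the drop-out rate and the target therefore cannot all be right, whatever effect size or SD one believes.

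What is at stake is the headline power claim. Readers of a null result would take it as coming from a trial with 80% power for an 8-point MADRS difference, when the trial's own drop-out assumption gives less. Treatment estimates and confidence intervals are not affected.

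**Working it through.** **Inputs** (from *Sample size and feasibility of recruitment* unless noted)

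- Difference 8, SD 10, so d = 8/10 = 0.8
- Two-sided alpha 0.05, independent-samples t-test, target power 80%
- Required total 56, drop-out 40%, recruitment target 78
- 1:1 allocation (assumption, from the two arms and block generator in *Randomization*)

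**Step 1: can the 56 be reproduced?** Exact power of the t-test comes from the non-central t distribution with n₁ + n₂ − 2 degrees of freedom and non-centrality d/√(1/n₁ + 1/n₂).

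| Per arm | Total | Non-centrality | Power |
|---|---|---|---|
| 25 | 50 | 2.83 | 79.1% |
| 26 | 52 | 2.88 | 80.7% |
| 28 | 56 | 2.99 | 83.6% |

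The stated inputs need 52. The normal approximation needs 50. Other variants, by the normal approximation, also miss 56: one-sided testing gives 40, 85% power gives 58 and 90% power gives 66. So 56 errs on the safe side, but it is not the 80% figure.

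**Step 2: can the 78 be reproduced?**

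- Correct inflation: n/(1 − 0.40) = 56/0.6 = 93.3, so 94 (47 per arm).
- Multiplication: 56 × 1.4 = 78.4, which matches 78.
- Starting from 52: 52/0.6 = 86.7, so 87 (88 with equal arms).
- Starting from 50: 50/0.6 = 83.3, so 84.

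Dividing 50, 52 or 56 by 0.6 never gives 78.

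**Step 3: what does 78 deliver at 40% drop-out?** 78 × 0.6 = 46.8, about 23 to 24 per arm.

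| Completers | Power, t-test | Power, normal approximation |
|---|---|---|
| 23 + 23 | 75.6% | 77.4% |
| 23 + 24 | 76.5% | 78.3% |
| 24 + 24 | 77.4% | 79.1% |

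None of these reaches 80% by either method. At 23.4 per arm, the difference detectable with 80% power on the t-test is 8.37 points.

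**Step 4: what drop-out can 78 tolerate?**

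- To keep 56: 1 − 56/78 = 28.2%.
- To keep 52, the true 80% requirement: 1 − 52/78 = 33.3%.

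**The case against.** The strongest objection is that the 76% belongs to a completers-only t-test, while the *Statistical analysis plan* section makes a likelihood-based mixed model on all available visits the primary analysis. Drop-outs with earlier scores would add information. As an illustration on assumed inputs, suppose every drop-out has one earlier post-baseline score, data are missing at random, and that score correlates r with the week-20 change. The effective total is then 78/(r² + (1 − r²)/0.6):

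- r = 0.3 gives 48.5, power 77.9%
- r = 0.4 gives 50, power 79.1%
- r = 0.5 gives 52, power 80.7%

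This stands as a caveat: a power below 80% is shown for the planning test, not for the mixed model. It does not rescue the stated figures. The plan sizes on a t-test, inflates explicitly for drop-out, claims no gain from the model and gives no correlation from which to compute one. Anyone lost before week 2 would contribute nothing of this kind.

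Four smaller points:

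- **Size.** The loss is about 3.5 points on the t-test (80 − 76.5) and 1.7 by the normal approximation (80 − 78.3). At the 10.9-point difference implied by the cited prior trial (10.0 + 0.9), with SD 10, 23 + 24 completers give about 95% power. This is fair, and it limits how much weight the point carries, but the plan chose 8 as its design value.
- **The 56.** If blocks hold eight, 56 = 7 × 8 is the smallest whole number of blocks that covers 52. The article does not give this reason, but it is possible, so 56 need not be a mistake. Its power still needs to be stated correctly.
- **The multiplier.** That 1.4 was used is an inference from the fit. The inconsistency does not depend on it.
- **Misreading a null result.** This is a risk, not a certainty, since estimates and intervals will carry their own precision.

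**Conclusion.** The concern holds. The 56, the 40% and the 78 cannot be reconciled: at 40% loss the target leaves about 47, which is 9 short of the plan's own requirement and 5 short of the 52 that its inputs need for 80% power. Against a correct inflation of 56, recruitment is 16 too low (94 − 78). Power on the named test is 75.6% to 76.5% with 46 or 47 completers.

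The arithmetic contradiction rests on no assumption. The power figures assume 1:1 allocation, SD 10, a true difference of 8 and analysis of completers only. The shortfall in power is modest, but a stated design figure is wrong under the plan's own assumption and should be corrected.

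**What to change.** Restate the figures; enrolment need not change. Either of these would do:

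- 78 randomised; with 40% drop-out about 47 are evaluable at week 20, giving about 76% power for a difference of 8 with SD 10 on a two-sided 5% t-test.
- 78 randomised gives 80% power if drop-out is at most 33% (52 evaluable), and 56 evaluable if it is at most 28%.

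In the same paragraph, either replace 56 with 52 as the number for 80% power, or keep 56, say that it corresponds to about 84% power and give the reason for choosing it. If a gain from the baseline-adjusted mixed model is to be claimed, compute it and state the assumed correlations and drop-out timing.

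If the sponsor would rather keep both the 40% assumption and the 80% claim, the target must rise to 87 (88 with equal arms), or to 94 to retain 56.

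Restating costs a few lines of text and a slightly less favourable power figure. It changes no visit, participant or analysis.
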